### Statistical analysis

#### Populations for analysis

The Intent to Treat (ITT) population is defined as all eligible participants who participated in Visit 1 (screening) and Visit 2 (randomisation); all efficacy and safety analyses will be performed on this population. The per protocol population (PP) will include all participants of the ITT group who completed all scheduled visits without any major protocol deviations. Participants must complete at least 80% of all bG measurements of the 3-day glycaemic profile form to be included in the PP analysis.

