### Participants

The study will recruit 226 T1DM and T2DM patients who have been using MDI therapy for at least 6 months. Participants will be enrolled and randomised to the experimental (EXP) or control (CNL) groups; 113 participants in each group. This will lead to a total of 90 participants completing each arm at 6 months, assuming a drop-out rate of 20%.

Key inclusion criteria are: ≥18 years of age; T1DM or T2DM treated with MDI therapy for ≥6 months; HbA1c #62;7.5%; adjusts meal insulin doses based on CHO content of meal; and has completed CHO training within last 2 years. Key exclusion criteria are: NPH or pre-mixed insulin; treated with anti-diabetic agents (except metformin); use of fixed-dose therapy; or use of sliding scale insulin doses determined exclusively on specific bG results. The complete list of inclusion and exclusion criteria is presented in Table 1.

**Table 1 T1:** Inclusion and exclusion criteria

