#### Visit 2: randomisation and intensive monitoring (week – minus 1)

At Visit 2, investigators will collect participants’ bG meters, completed 3-day glycaemic profiles and CGM devices (if applicable). Investigators will upload bG meter data via the research version of the Accu-Chek® SmartPix device (Roche Diagnostics, Indianapolis, Indiana, USA). When applicable, CGM data will also be uploaded to the server. Blood glucose data will be downloaded to clinic software, using either the commercial Accu-Chek® Smart Pix device or Accu-Chek® 360˚ View diabetes management system software (Roche Diagnostics, Indianapolis, Indiana, USA), and investigators will prepare printouts to review with each participant. New adverse events (AEs) and significant adverse events (SAEs), or changes in ongoing AEs/SAEs since the last visit, will be assessed and recorded; participants’ concomitant medications will be updated.

Investigators will then conduct MDI and CHO counting training, which will be individualised to address each participant’s knowledge and/or skills deficits as identified during the MDI therapy and CHO counting assessments performed at Visit 1. Standardised checklists will be used to document participant competencies. Participants must be competent in both MDI therapy and CHO counting knowledge in order to continue in the study. Following this training, participants will be randomised to the control group (CNL) for usual care or to bolus advisor use (EXP). EXP participants will be given automated bolus advisor training materials for review at home.

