### Measures

#### Primary endpoint

HbA1c: The primary endpoint of the study is glycaemic control, as assessed by change in HbA1c from baseline over 6 months specifically, looking at number of patients who achieved #62;0.5% HbA1c reduction at study end. Blood samples will be collected at screening and Visits 6 (week 11) and 9 (week 24). HbA1c analysis will be conducted by a central laboratory, using HPLC methodology (VII Turbo haemoglobin testing system, Bio-Rad Laboratories, Hercules, California, USA).

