#### Primary outcome analysis

Anticipated attrition of 20% will yield a sample size of 180 (90 per study group), which will provide #62;80% power to detect a mean difference of 0.5% in change in HbA1c, with SD of 0.9%. The absolute and relative change in HbA1c from baseline to study end for the CNL and EXP groups will compared using the two-sample *t*-test for the pooled ITT population. These tests will be performed at the one-sided 5% level of significance for rejecting the null hypothesis of no difference or a difference in favor of the CNL group. An analysis of covariance with the binary covariables (study group, sex and diabetes type) and the continuous baseline covariables (HbA1c, age and CHO counting assessment score) will be performed for the absolute and relative HbA1c change. Additional separate analyses of (co)variance will be performed using two explanatory variables (study group and one adjusting covariable) for the above mentioned covariables and other baseline covariables (e.g., country, center, time since diabetes diagnosis, existing diabetes related diseases, time since MDI start, bG measures from SMBG at baseline, frequencies of hypoglycaemia at baseline, laboratory parameters and, summary scores from psychosocial questionnaires) for the pooled groups. The one-sided 95% confidence intervals of the HbA1c change for CNL and EXP groups and the difference between the groups will also be calculated for the pooled groups.

Summary statistics (N, mean, median, SD, lower and upper quartile, minimum and maximum) will be provided for the observed HbA1c values by study group for each applicable scheduled visit (Visits 1, 6 and 9). Graphical techniques will be used to display the HbA1c change over time.

Pearson correlation coefficients will be computed for the HbA1c values at Visits 1, 6, and 9 and the absolute and relative HbA1c changes from baseline to study end vs. demographic and clinical variables; bG measures from SMBG and CGM scores for each collection visit, other laboratory parameters, frequencies of hypoglycaemia, CHO scores; and summary scores from psychosocial questionnaires. For all of these covariables, the correlation coefficients for their changes from baseline vs. the HbA1c parameters will be computed, too. Additionally, the correlation coefficients for the HbA1c parameters vs. bolus advisor parameters will be computed for the EXP group.

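### The primary t-test on change to week 24 does not match the declared ITT population: about 46 of 226 participants have no stated way into it, and week-11 HbA1c is left out of the group comparison

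*Protocol article*

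**What the plan says.** All references are to the protocol article.

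- **Populations for analysis.** The ITT population "is defined as all eligible participants who participated in Visit 1 (screening) and Visit 2 (randomisation"). All efficacy and safety analyses are assigned to it, and no post-baseline HbA1c is required for membership. The per-protocol set additionally demands that all scheduled visits were completed.
- **Primary outcome analysis.** Absolute and relative HbA1c change from baseline to study end is compared between groups with a two-sample t-test in the pooled ITT population. "These tests will be performed at the one-sided 5% level of significance". The analyses of covariance use the same change scores.
- **Sizing.** "The study will recruit 226 T1DM and T2DM patients who have been using MDI therapy for at least 6 months" (Participants). "This will lead to a total of 90 participants completing each arm at 6 months, assuming a drop-out rate of 20"% (same section). The Primary outcome analysis section repeats it: "Anticipated attrition of 20% will yield a sample size of 180 (90 per study group").
- **HbA1c measurements.** "Blood samples will be collected at screening and Visits 6 (week 11) and 9 (week 24") (Primary endpoint). In the analysis section the Visit 6 value appears in summary statistics, graphs and correlations, but not in the comparison of the groups.

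**The concern.** A change score to study end exists only for a participant with a Visit 9 HbA1c. The declared population does not require that value, the declared test does, and the sample size is built on the number expected to have it. The article does not reconcile the three. If nothing is filled in, neither the ITT nor the per-protocol analysis lets dropouts inform the primary contrast, even where their week-11 HbA1c is on file.

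Only one arm receives the new device, so participants know their assignment, and reasons for leaving may differ between arms. If poor responders leave one arm more than the other, those who remain are no longer comparable. At stake is the validity of the primary comparison: a false-positive rate above the nominal 5% if the bias favours the bolus-advisor arm (EXP), or a true benefit partly hidden if it favours control (CNL).

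**Working it through.** **1. Inputs from the article.** Difference 0.5, SD 0.9, one-sided 5% level, 90 per arm analysed, 113 per arm randomised, 20% dropout.

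**2. The article's own figures reproduce.**
- Inflation for dropout: 90 / (1 − 0.20) = 112.5, rounded up to 113 per arm, 226 in total.
- Expected without a Visit 9 value: 226 − 180 = 46 (20.4%).
- Standard error at 90 per arm: 0.9 × √(2/90) = 0.134. Power = Φ(0.5/0.134 − 1.645) = 98.1%, which satisfies the stated claim of more than 80%.
- With all 226 contributing: standard error 0.9 × √(2/113) = 0.120, power 99.4%.

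Losing 46 participants costs about one point of power. The question is bias.

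**3. When a completer contrast is biased.** Let d be the dropout rate in an arm and g the amount by which dropouts' HbA1c change is worse than completers'. The full-arm mean is then the completer mean plus d × g, so

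bias towards EXP = d(EXP) × g(EXP) − d(CNL) × g(CNL).

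The article gives no value for g or for the split of dropout, so these are assumptions:

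| Dropout EXP / CNL | g EXP / CNL | Bias towards EXP |
|---|---|---|
| 20% / 20% | 0.5 / 0.5 | 0 |
| 25% / 15% | 0 / 0 | 0 |
| 25% / 15% | 0.5 / 0.5 | 0.05 |
| 30% / 10% | 0.5 / 0.5 | 0.10 |
| 20% / 20% | 0.5 / 0 | 0.10 |
| 15% / 25% | 0.5 / 0.5 | −0.05 |

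Unequal rates alone do nothing (second row), and equal rates do not protect (fifth row).

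**4. Effect on the one-sided error under a true null.** Error = 1 − Φ(1.645 − bias/0.134).
- Bias 0.05: 10%.
- Bias 0.10: 18%.
- Bias 0.18: 38%.
- Bias −0.11: 0.7%.

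**5. Simulation under a true null.** Set-up: 113 per arm, SD 0.9, week 11/week 24 correlation 0.7, 20% dropout in each arm, and log-odds of dropout rising with poor week-11 response by a given slope per SD. Slopes of 0.5 to 2 are odds ratios of about 1.6 to 7.4. There were 4,000 to 6,000 trials per scenario, and ranges cover repeated runs.

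| Slope EXP / CNL | Completer bias towards EXP | One-sided rejection |
|---|---|---|
| 0.5 / 0 | 0.06 | 11–12% |
| 1 / 0 | 0.11 | 21–22% |
| 1.5 / 0 | 0.14 | 28–29% |
| 2 / 0 | 0.16–0.17 | 34–36% |
| 1 / 0.5 | 0.05 | 9–10% |
| 1 / 1 | 0.00 | about 5% |
| 0 / 1 | −0.11 | 0.7% |

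With correlation 0.5, the EXP-only scenarios give a bias of 0.04 to 0.12 and rejection of 9% to 23%.

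**6. What the week-11 value recovers.** In these scenarios every dropout has a week-11 HbA1c, and dropout depends only on that value. A likelihood-type estimate using it then has bias within 0.004, but this follows from the set-up. If half the dropouts leave before week 11 (assumed), its bias is about 0.05 at slope 1 and 0.07 to 0.08 at slope 2, against 0.11 and 0.16 to 0.17 for completers. The model then removes only about half of the bias.

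**The case against.** The strongest reply is that the core is an omission. A reader might infer that dropouts are excluded and that the ITT result is really a completer result. The article says neither. A rule for a missing Visit 9 HbA1c, including one that uses week 11, may stand in a full protocol or SAP that is not shown, and its absence from an article is no finding. This stands, so the point is confined to what is stated: a population, a test and a sample size that do not fit together, and a measured week-11 value given no part in the group comparison. Sizing on completers is routine and does not by itself fix who is analysed.

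The magnitude also depends on chosen scenarios. A reader might infer that differential dropout as such biases the result, or that the bias must favour EXP. Neither follows. Dropout must be related to HbA1c response, and controls who do badly without a device may be the ones who leave, which reverses the sign.

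On the definition, a reader might infer that people who were never randomised enter the ITT set, because of the Visit 2 rule: "Participants must be competent in both MDI therapy and CHO counting knowledge in order to continue in the study". This is strained. Randomisation follows that check, so someone who fails it has no group and cannot enter a two-group test. Likewise, eligibility is confirmed at Visit 1, and no passage provides for removal after randomisation. What remains is a gain in clarity from naming randomisation as the criterion.

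Finally, the choice of a repeated-measures model over a t-test is partly a preference. It is justified here because it uses data already collected for participants whom the t-test cannot use.

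**Conclusion.** The point holds in limited form. The stated primary test suits the stated population badly: without a fill-in rule not shown here, about 46 of 226 participants cannot contribute to it, and the week-11 HbA1c does not enter the comparison.

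The consequence is conditional. With response-related dropout in one arm only, SD 0.9, correlation 0.7 and 20% dropout per arm, the bias is about 0.06 to 0.17 HbA1c points, against a target difference of 0.5. The one-sided error is 11% to 36% when the bias favours EXP and about 1% when it favours CNL (slope 1). With the same mechanism and rate in both arms it is zero. The slopes, the correlation and the timing of dropout are assumptions. The documents do not show that such dropout will occur or in which direction it would act.

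The sample-size figures are correct and power is ample either way.

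**What to change.** 1. Define ITT as all randomised participants, analysed in the group to which they were assigned.
2. Make the primary estimate the Visit 9 group contrast from a repeated-measures model of HbA1c change at Visits 6 and 9. Include group-by-visit and baseline HbA1c-by-visit terms and the other covariates already named for the main analysis of covariance (sex, diabetes type, age, CHO counting score).
3. Keep the two-sample t-test on change to study end as a supportive analysis.
4. Add one sensitivity analysis for data not missing at random, for example control-based imputation. It is needed because participants who leave before week 11 have no post-baseline HbA1c, and the model only partly removes the bias that they cause.

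Cost: a change of wording and slightly more programming, with no new visits or samples. The downside is that the primary estimate then relies on data being missing at random, which the sensitivity analysis is there to probe.

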#### Primary outcome analysis

Anticipated attrition of 20% will yield a sample size of 180 (90 per study group), which will provide #62;80% power to detect a mean difference of 0.5% in change in HbA1c, with SD of 0.9%. The absolute and relative change in HbA1c from baseline to study end for the CNL and EXP groups will compared using the two-sample *t*-test for the pooled ITT population. These tests will be performed at the one-sided 5% level of significance for rejecting the null hypothesis of no difference or a difference in favor of the CNL group. An analysis of covariance with the binary covariables (study group, sex and diabetes type) and the continuous baseline covariables (HbA1c, age and CHO counting assessment score) will be performed for the absolute and relative HbA1c change. Additional separate analyses of (co)variance will be performed using two explanatory variables (study group and one adjusting covariable) for the above mentioned covariables and other baseline covariables (e.g., country, center, time since diabetes diagnosis, existing diabetes related diseases, time since MDI start, bG measures from SMBG at baseline, frequencies of hypoglycaemia at baseline, laboratory parameters and, summary scores from psychosocial questionnaires) for the pooled groups. The one-sided 95% confidence intervals of the HbA1c change for CNL and EXP groups and the difference between the groups will also be calculated for the pooled groups.

Summary statistics (N, mean, median, SD, lower and upper quartile, minimum and maximum) will be provided for the observed HbA1c values by study group for each applicable scheduled visit (Visits 1, 6 and 9). Graphical techniques will be used to display the HbA1c change over time.

Pearson correlation coefficients will be computed for the HbA1c values at Visits 1, 6, and 9 and the absolute and relative HbA1c changes from baseline to study end vs. demographic and clinical variables; bG measures from SMBG and CGM scores for each collection visit, other laboratory parameters, frequencies of hypoglycaemia, CHO scores; and summary scores from psychosocial questionnaires. For all of these covariables, the correlation coefficients for their changes from baseline vs. the HbA1c parameters will be computed, too. Additionally, the correlation coefficients for the HbA1c parameters vs. bolus advisor parameters will be computed for the EXP group.

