#### Visits 5 through 9 (weeks – 4 through 24)

At Visits 5 through 9, investigators will collect participants’ bG meters, upload bG meter data to a secure server; download meters to clinic software, and prepare printouts of bG data to review with participants. New AE/SAEs or changes to ongoing AE/SAEs since the last visit will be assessed and concomitant medications will be updated. At Visits 5, 7 and 9, participants’ 3-day glycaemic profiles and historic data will be collected and reviewed to adjust therapy parameters (if needed). If parameters are adjusted, participants’ automated bolus advisor devices will be updated with the new parameters. HbA1c samples will be collected at Visits 6 and 9. Additional laboratory samples will be obtained at Visit 9 for chemistry profile and lipid profile, FBC, perform dipstick urinalysis. At Visits 7 and 9, 5-day CGM data will be uploaded to the secure server. Patient questionnaires will be administered at Visits 7 and 9. Final CHO counting and MDI therapy assessments will be conducted at Visit 9.

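### As written, the primary ITT comparison can include only participants with a week-24 HbA1c; the week-11 HbA1c enters no between-group test, so arm-specific dropout could bias the result in either direction

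*Protocol article*

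**What the plan says.** - **Population.** The Populations for analysis section defines ITT by eligibility and attendance at Visits 1 and 2. No post-baseline measurement is needed. Of this set it says that "all efficacy and safety analyses will be performed on this population".
- **Primary test.** The Primary outcome analysis section compares absolute and relative HbA1c change from baseline to study end by two-sample t-test in the pooled ITT population. An ANCOVA of the same change scores follows. On the error rate: "These tests will be performed at the one-sided 5% level of significance".
- **Sample size.** The same section states: "Anticipated attrition of 20% will yield a sample size of 180 (90 per study group". The Participants section gives 113 randomised per arm and 90 per arm finishing at 6 months.
- **HbA1c schedule.** After screening, "HbA1c samples will be collected at Visits 6 and 9". The Primary endpoint section places these at weeks 11 and 24 and sends them to a central laboratory.
- **Use of week 11.** Summary statistics "will be provided for the observed HbA1c values by study group for each applicable scheduled visit (Visits 1, 6 and 9"; change over time is graphed, and Pearson correlations include the Visit 6 value. No stated comparison between the groups uses it.

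**The concern.** A change from baseline to week 24 exists only for someone with a week-24 HbA1c. If nothing fills the gap, the stated test covers about 180 of 226 randomised participants, although the named population is all of them. The per-protocol set already requires every scheduled visit. Both sets would then leave out the people who dropped out, and comparing ITT with per-protocol results could not show whether dropout matters.

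Participants know their arm, because only EXP receives the advisor. Reasons for leaving may therefore differ between arms. If they are related to glycaemic response, the comparison of those remaining is no longer the randomised comparison, and the error falls on the primary result. Many of those who leave late will already have given a week-11 HbA1c, which says something about how they were doing, yet the stated test does not use it.

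**Working it through.** **1. The plan's own figures.** The inputs are 113 per arm, 20% dropout, a difference of 0.5, an SD of change of 0.9 and one-sided alpha of 0.05, all from the article.

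- 226 × 0.8 = 180.8, so 180 of 226 is right; 226 − 180 = 46 (20.4%).
- Standard error with 90 per arm: 0.9 × √(2/90) = 0.134.
- Power: Φ(0.5/0.134 − 1.645) = Φ(2.08) = 98.1%, consistent with the stated inequality.
- If all 226 were analysed and the 20% who drop out had no benefit, the difference would be 0.8 × 0.5 = 0.4, with standard error 0.9 × √(2/113) = 0.120 and power of about 95.5%. Power is not the problem.

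**2. From dropout to bias.** Suppose that in one arm those lost would have had a change worse by D than those remaining, with no such difference in the other arm. The bias in the group difference is then 0.20 × D. With no true effect, the one-sided rejection rate is 1 − Φ(1.645 − bias/0.134) if the loss is in EXP, and 1 − Φ(1.645 + bias/0.134) if it is in CNL.

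| Bias (HbA1c percentage points) | Bias/SE | Rejection, loss in EXP | Rejection, loss in CNL |
|---|---|---|---|
| 0 | 0 | 5% | 5% |
| 0.06 | 0.45 | 11.5% | 1.8% |
| 0.10 | 0.75 | 18.4% | 0.8% |

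**3. How large a bias is plausible?** The article gives neither a dropout mechanism nor a correlation between week-11 and week-24 change, so both are assumed. The simulations used 113 per arm, SD 0.9 at both visits, 20% lost per arm, no true effect and a correlation of 0.5 to 0.8. Where loss was selective, the odds of leaving rose 2.7-fold per SD of poorer week-11 change.

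| Loss | Bias of t-test on observed week-24 change | One-sided rejection |
|---|---|---|
| Random in both arms | about 0 | about 5% |
| Same selection in both arms | about 0 | about 5% |
| Selective in EXP only, about three quarters of the loss after week 11 | +0.06 to +0.10 | about 11 to 18% |
| Selective in CNL only, same split | −0.06 to −0.10 | about 1 to 2% |
| Selective in EXP only, all loss driven by week-11 change | +0.08 to +0.13 | 16 to 25% |

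Positive values favour EXP. The rejection rates in the third and fourth rows agree with the formula in step 2.

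**4. Using week 11.** A likelihood estimate that uses the week-11 value had bias near zero and rejected in about 5% of trials in all of these scenarios, with an equal or slightly smaller standard error. In each of them dropout depended only on observed data, which is the condition under which such a model is unbiased.

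**The case against.** The strongest reply is that the article nowhere restricts the test to completers. It names the ITT population. How a member without a week-24 value enters is commonly left to the full protocol or SAP, neither of which is shown. A t-test of change in an ITT set is compatible with an imputation rule, and such a rule could use week 11. The figure of 180 is ordinary inflation for dropout and does not define the analysis set. All of this stands. It limits the point to what the stated method does when applied as written, and it lowers the severity.

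Three stronger readings are tempting, and the documents do not support them:

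- **That the plan leaves the week-11 HbA1c unused.** It is summarised, plotted and correlated; it is absent only from the between-group tests.
- **That the main result is biased, and in favour of the advisor.** Bias needs outcome-related dropout that differs between arms. Both arms receive intensive management and the same assessments, and no passage shows that poor responders leave EXP more often. Selection in CNL would bias the result against the advisor.
- **That people who stop using the device are lost.** Visit 9 sampling carries no condition on device use.

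It is also fair to say that the simulations suit the proposed model, since loss was generated from observed week-11 change. The model would not protect against unobserved selection or against selective loss before week 11.

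**Conclusion.** The point holds conditionally, at moderate severity. The stated population needs no post-baseline HbA1c, while the stated test can use only people with a week-24 value. With 20% loss, the gap is large enough to matter if selection differs by arm: about 0.06 to 0.10 percentage points under the one-arm assumptions in the third and fourth rows, against a target difference of 0.5. One-sided error moves from 5% to about 11 to 18% if the selective loss is in EXP, or to about 1 to 2% if it is in CNL. Neither the direction nor the size can be read from the documents, and both are nil if loss is random or alike in the two arms.

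The case for change does not depend on predicting which of these will occur. A method that uses the week-11 data is robust to more dropout patterns, at no loss of precision. If the SAP already has a missing-data rule, the remaining task is to align the primary-analysis text with it.

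**What to change.** - **Primary analysis of mean HbA1c change.** Use a likelihood-based repeated-measures model on HbA1c at Visits 6 and 9 for all randomised participants, with group-by-visit, baseline HbA1c-by-visit and the covariates already listed. The EXP–CNL difference at week 24 is the primary contrast.
- **Sensitivity analyses.** Keep the t-test and ANCOVA on observed week-24 values. Add one delta-adjusted analysis, in which missing outcomes are shifted away from the model's prediction, to cover missingness that observed data do not explain.
- **Wording.** State in the population and primary-analysis sections how an ITT participant without a week-24 HbA1c enters.

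The cost is wording and a modest amount of analysis; the week-11 samples are already scheduled. The downside is small: the model assumes that missingness is explained by observed data, which the delta-adjusted analysis probes but cannot verify. This change concerns mean change only. The Primary endpoint section also mentions the number of patients reaching a set reduction, and a model for means does not address that.

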*Participant Adherence/Use of Rule Sets:* Changes in participants’ therapy adherence to and use of rule sets in EXP participants will be derived from downloaded data obtained from automated bolus advisor devices. Adherence in CNL participants will be derived from documented therapy parameters and participants’ diaries, which are included in 3-day glycaemic profile forms. These assessments will be used to determine if participants’ adherence/use of rule sets correlates with improvement in glycaemic control. Analyses will include: average number of correctly and incorrectly used insulin-to-carbohydrate (I:CHO) rules per day for CHO intake; average number of correctly and incorrectly used insulin sensitivity factor (ISF) rules per day for bG adjustment; and number of changed I:CHO and ISF parameters compared to therapy parameters at study start (Visit 3). Data will be collected at Visits 2 (week minus 2), 5 (week 4), 7 (week 12) and 9 (week 24).

*CHO Counting:* Changes from baseline in participants’ ability to accurately count CHO will be assessed using the DAFNE plate assessment scores from Visit 1 (week minus 2) and 9 (week 24). This assessment will be used to determine if participants’ CHO counting skills correlates with improvement in glycaemic control.

*Psychosocial Outcomes*: Psychosocial outcomes including treatment satisfaction, social functioning and factors important to quality of life will be assessed using the participant questionnaire, which incorporates questions from validated psychometric instruments, as well as commonly used survey questions, to assess depression, diabetes-specific distress, diabetes self-efficacy, treatment satisfaction, health outcomes and fear of hypoglycaemia. Participant questionnaire items include: Patient Health Questionnaire depression scale (PHQ-8) [25]; Problem Area in Diabetes (PAID) [26]; Hypoglycaemia Fear Scale (HFS –II) [11];Diabetes Treatment Satisfaction Questionnaire (DTSQs, [baseline] and DTSQc [change]) [27];Gold Scale [28];and EuroQol-5 Dimensions-5 Levels measure (EQ-5D-5L) [29] (Table 2). The questionnaires will be administered at Visits 1 (week minus 2), 7 (week 12) and 9 (week 24); however, the DTSQs and DTSQc portions will be administered only at Visits 1 and 9.

**Table 2 T2:** Participant Questionnaire components

**Instrument**	**Description**	**Scoring**

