#### Secondary outcome analyses

Statistical analysis of change in time spent within target range will be performed according to the same schemata used for the primary outcome. Other secondary outcome variables will be compared descriptively by study groups for each scheduled visit and for changes between visits. Continuous variables, including scores from the questionnaires will be summarised using N, mean, SD, median, lower and upper quartile, minimum and maximum; categorical variables will be summarised using counts and percentages of participants in each category. Two-sample t-tests in the case of continuous variables and chi-square tests in the case of categorical variables will be performed for group comparisons. Graphical techniques will be used to display changes over time, if appropriate. Pearson correlation coefficients will be computed between all variables of interest.

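### On-study adherence and carbohydrate-counting measures are to be related to HbA1c improvement by unadjusted Pearson correlation, which picks up any arm difference when the arms are pooled

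*Protocol article*

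**What the plan says.** The Primary outcome analysis section states: "Pearson correlation coefficients will be computed for the HbA1c values at Visits 1, 6, and 9 and the absolute and relative HbA1c changes". The pairing for the changes reads "the absolute and relative HbA1c changes from baseline to study end vs. demographic and clinical variables", and the list goes on to glucose measures from each collection visit, laboratory values, hypoglycaemia frequencies, carbohydrate (CHO) scores and questionnaire summary scores. It continues: "For all of these covariables, the correlation coefficients for their changes from baseline vs. the HbA1c parameters will be computed, too". One set is confined to a single arm: "the correlation coefficients for the HbA1c parameters vs. bolus advisor parameters will be computed for the EXP group". The Secondary outcome analyses section then adds: "Pearson correlation coefficients will be computed between all variables of interest".

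The Secondary endpoints section says what two of these relations are for. On adherence: "These assessments will be used to determine if participants’ adherence/use of rule sets correlates with improvement in glycaemic control". On CHO counting: "This assessment will be used to determine if participants’ CHO counting skills correlates with improvement in glycaemic control". It also says that adherence comes from bolus advisor downloads in EXP, but from documented parameters and diaries in CNL.

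Adjusted models of HbA1c change are planned in the Primary outcome analysis section. One is a joint ANCOVA with study group, sex, diabetes type, and baseline HbA1c, age and CHO score. The others are separate models, each with study group and one baseline covariable.

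**The concern.** The adherence and CHO-counting questions concern on-study behaviour and change in skill. The adjusted models contain baseline covariables only, so nothing but the raw correlation is named for relating post-baseline values to HbA1c change. CHO scores and their changes are listed explicitly. Adherence is not listed, and comes in through the general sentence on all variables of interest.

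If the device lowers HbA1c, any post-baseline variable that also differs by arm will correlate with HbA1c change in the pooled sample, even if no one's improvement depends on it within an arm. Adherence is the most exposed variable, because its source differs by arm: a pure measurement difference between download and diary would be enough. The trial could then report that better adherence goes with better control when the coefficient only restates which arm people were in.

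A second mechanism concerns baseline variables. HbA1c change contains baseline HbA1c. A baseline glucose measure that shares its short-term fluctuation may correlate with the later fall through regression to the mean, and the one-covariable models omit baseline HbA1c unless it is itself the covariable.

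**Working it through.** The article states no figure for the correlations. The inputs it gives (Primary outcome analysis) are a difference in HbA1c change of 0.5, an SD of 0.9 and 180 completers, 90 per arm. As a check on them: 0.5 / (0.9 × √(2/90)) = 3.73; 3.73 − 1.645 = 2.08; one-sided power 98%. The stated bound of more than 80% is therefore true. For dropout, 113 × 0.8 = 90.4 per arm, which agrees with the plan.

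**Arm difference alone.** Let d1 be the arm difference in HbA1c change and d2 the arm difference in the other variable, each in within-arm SDs, with no association within arm and 1:1 allocation. The size of the pooled correlation is

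r = (d1·d2/4) / √[(1 + d1²/4)(1 + d2²/4)].

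Here d1 = 0.5/0.9 = 0.556, so 1 + d1²/4 = 1.077. The document does not give d2; 0.5, 1 and 2 are assumed. As a yardstick, the last column is the chance of passing a two-sided 5% test of r at N = 180 (Fisher z, standard error 1/√177; critical size of r 0.146).

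| Assumed d2 | Calculation | Size of r | Chance of passing 5% |
|---|---|---|---|
| 0 | 0 | 0 | 5% |
| 0.5 | 0.0694 / √(1.077 × 1.0625) | 0.06 | 14% |
| 1 | 0.1389 / √(1.077 × 1.25) | 0.12 | 36% |
| 2 | 0.2778 / √(1.077 × 2) | 0.19 | 72% |

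Simulation (4,000 trials of 180 people) gave 14% and 35% for shifts of 0.5 and 1 SD. After partialling out study group and baseline HbA1c, the mean r was about 0 and the rates were 5.1% and 4.6%. Conditioning on study group alone is enough for this artefact, since within arm the two variables are unrelated by construction. A baseline variable unrelated to HbA1c had mean r of 0.00 and a rate of about 5% with no adjustment, because randomisation balances it.

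**Regression to the mean.** Assume the same SD, s, for HbA1c at baseline and at study end (not in the document). With SD of change 0.9:

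- Correlation of baseline with final HbA1c: 1 − 0.81/(2s²).
- Correlation of baseline HbA1c with change: −0.9/(2s). This is −0.56, −0.45 and −0.30 for s = 0.8, 1.0 and 1.5.
- A covariable correlated 0.5 (assumed) with baseline HbA1c, with no other link to outcome, gets half of that: −0.28, −0.22 and −0.15. At s = 1.0 the simulated rate of passing 5% was 84%. With baseline HbA1c and study group partialled out it was 5%.

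**Where this mechanism does not act.** Take s = 1.0, so baseline and final HbA1c correlate 0.595, and let a covariable correlate 0.5 with both, that is, track only the stable level. Its raw correlation with change is 0. Its partial correlation with final HbA1c given baseline is (0.5 − 0.5 × 0.595) / √[(1 − 0.5²)(1 − 0.595²)] = 0.2025 / √(0.75 × 0.646) = 0.29. Here baseline adjustment produces an association that the raw coefficient does not show.

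**The case against.** The strongest reply is that adjusted analyses are planned. For baseline CHO score, the joint ANCOVA already adjusts for baseline HbA1c and study group. Baseline glucose, hypoglycaemia, laboratory and questionnaire measures each get a model with study group. A reader might infer that the trial will judge everything related to improvement from raw correlations; the document does not support that. The reply does not reach post-baseline adherence or change in CHO score, for which no adjusted model is named.

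Second, pooling is inferred. The restriction to EXP for bolus advisor parameters is forced, since only EXP has the device, so it says little about the rest. By-arm reporting could sit in the full protocol or SAP. That stands as a caution, although pooling remains the natural reading of the text.

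Third, a reader might infer that any covariable tracking baseline HbA1c must show a spurious correlation. That is too broad: it requires shared short-term variation, and for a stable-level covariable the baseline adjustment is what creates the association. Baseline adjustment therefore belongs beside the raw value, not in its place.

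Fourth, the correlations carry no test, threshold or decision rule, so the percentages above are a yardstick and not error rates of a planned test. This also stands. Preferring rank correlations for counts or single-item scales is a matter of taste and is not pressed.

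**Conclusion.** The point holds in a limited form and is minor. For post-baseline variables that differ by arm, the only method named for relating them to HbA1c change cannot separate a within-arm relation from the arm difference. The induced r is about 0.06 to 0.19 for assumed shifts of 0.5 to 2 SD, if the planned effect is true, the arms are pooled and 180 people contribute. Adherence is the clearest case because its source differs by arm. Whether CHO-counting change will differ by arm cannot be known from the document. The formula is for absolute change; relative change was not computed.

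Regression to the mean is a possible second artefact, confined to baseline measures that share short-term variation with baseline HbA1c. Its size rests on assumed SDs and correlations.

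A reader might go on to infer that the trial's main conclusion is at risk. It is not: the primary comparison is between randomised groups and does not use these correlations.

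**What to change.** - For post-baseline variables and their changes, report the correlation within each arm, or as a partial correlation or ANCOVA term given study group. Base the statements on adherence and CHO counting on that result.
- For covariables related to baseline HbA1c, show the estimate adjusted for baseline HbA1c beside the raw one, and say that the two rest on different assumptions.
- State whether the remaining correlations pool the arms, and label all raw Pearson coefficients descriptive and exploratory.

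This costs a few sentences in the analysis plan and a little programming, with no new data. The drawback is somewhat more output and probably fewer nominal associations to report.
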